   3. *Pre-assessment.* Next, pre-assessment is completed by administering the Life Events Checklist (LEC; (Gray, Litz, Hsu, & Lombardo, 2004)), the PTSD Checklist for DSM-5 (PCL-5, Weathers et al, 2013) and items derived from the Service Receipt Inventory (SRI; (Chisholm, Knapp, et al., 2000)).
2. Randomization
   1. Randomization will be carried out by an independent trial unit (at University of New South Wales) Randomization will be performed using computerised software on a 1:1 basis.
3. PM+ Intervention
   1. *Appointments.* CHW who will make contact with participants for treatment to begin. The first PM+ session will be scheduled within a few days and no longer than one week after the baseline assessment. This therapist will plan five consecutive meetings with the participant.
   2. *Additional instrument.* At the start of PM+ and at the beginning of every session the Psychological Outcome Profiles instrument (PSYCHLOPS; (Ashworth, 2004)) will be administered. This instrument, in contrast to above named instruments will be administered by the therapist *to assess and monitor* progress on problems for which the person seeks help.
4. Post intervention assessment
   1. *1-week follow-up.* The post-intervention assessment (WHODAS, GHQ-12, PCL-5) will be scheduled 7 weeks after the pre-intervention assessment (i.e., 1 week after the 5^th^ PM+ session).
   2. *3-month follow up.*  The follow-up assessment - with the same questionnaires plus the life events measure (LEC) and SRI items but without the treatment satisfaction questionnaire - will be scheduled at 3 months after the 5^th^ PM session.

All instruments will be administered by trained research staff blind to the allocation status of the participants. All independent assessors will receive a five day training in administering the instruments, in general interview techniques, and in responding to participant distress, including, as mentioned, psychological first aid.

*Statistical power and sample size*

Since Study Phase 1 is a small exploratory RCT with 40 participants (20 participants per group), that does not aim to detect statistically significant differences in effectiveness, no power calculations have been (or should be) carried out.

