In Study Phase 3 a total number of 346 participants will to be included. Since we are not aware of intervention studies that have been carried out in this population, and we expect the population to be heterogeneous with respect to the types of common health disorders, we aimed for a relatively conservatively estimated 50% reduction in GHQ-12 symptom score in the PM+ group as compared to a 30% reduction in the control group at 3 months after the conclusion of the study. These estimates are in line with the observed effectiveness of an intervention led by lay health counsellors for depressive and anxiety disorders in a landmark study in primary care in India (Patel et al, 2010). This corresponds with an odds ratio of for the PM+ intervention of 2,3. Power calculations suggest a minimum sample size of 133 participants per group (power = 0.95, alpha = 0.05, two-sided). Taking into account an expected 30% attrition at 3 months follow-up, we aim to include a total number of 346 participants (173 in the PM+ group and 173 in the care-as-usual control group).

*Measures*

The measures for use in this study are in Annex 6.

The below matrix gives an overview of the measures used in the RCT in terms of when they will be assessed and what concepts they assess.

| *Concept* | Pre-assessment measures | Post-treatment assessment measures | 3-months post-treatment follow-up assessment measures |
| --- | --- | --- | --- |
| 1. functioning | WHODAS (**screener)** | WHODAS | WHODAS |
| 1. distress | GHQ-12 (**screener** and **primary outcome**) | GHQ-12 | GHQ-12 |
| 1. adverse life events | LEC |  | LEC |
| 1. violence against women | WHO-VAQ |  |  |
| 1. PTSD | PCL-5 | PCL-5 | PCL-5 |
| 1. Cost of care | SRI items |  | SRI items |

1. WHODAS: socio-demographic information and disability

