Data on socio-demographic information (sex, age, education, marital status and work status) will be collected through questions A1-A5 of the WHO Disability Assessment Schedule 2.0 (WHODAS; [WHO, 2010a](#_ENREF_26)), which will be administered first. The WHODAS is a generic assessment instrument assessing health and disability. It is used across all diseases, including mental neurological and substance use disorders. It is simple to administer and applicable across cultures and can be used in all adult populations. WHODAS covers six domains (cognition, mobility, self-care, getting along, life activities, participation). It assesses difficulties people have due to their illness across these domains during the last 30 days. Difficulties are scored as none, mild, moderate, severe, or extreme. We will use the 12-item interviewer administered version. The WHODAS has been validated in Kenya (Chepngeno-Langat et al., 2011).

In analyses of Study Phase 3 data, the WHODAS will also be used to compute Quality Adjusted Life years, which is a measure of disease burden, for Study Phase 3 (Buttorff et al, 2012). Reference data for the female Kenyan population will be derived from the World Health Survey, in which Kenya was included (<http://apps.who.int/healthinfo/systems/surveydata/> index.php/catalog/80).

1. GHQ-12: distress

The primary outcome is level of psychological distress as measured by the General Health Questionnaire (GHQ-12; Goldberg & Williams, 1988; Jenkins et al., 2013) at 3 months follow-up (i.e., 3 months after the 5^th^ PM+ session). The GHQ-12 consists of 12 questions that are scored on a 4-point Likert scale ranging from 0 to 3..The total GHQ-12 score is obtained by summing up the scores of the individual items and ranges between 0-36 with higher scores representing higher levels of distress. When used as a screening tool, the GHQ-12 is usually scored bi-modally (i.e. - 0-0-1-1)., and ranges between 0-12. In a previous study in Kenya, a cut-off of higher than 2 has been reported to indicate clinical levels of distress (Jenkins et al., 2013).The GHQ has been widely used across low- and middle income countries, including Kenya (Jenkins et al., 2013).

1. LEC: exposure to potentially traumatic events (life events)

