**Data Management and Statistical Analysis**

The data, as collected by the interviewers (Study Phases 2 and 4) and independent assessors and PM+ providers (Study Phases 1 and 3) will be safely stored at the World Vision office of the field coordinator at Rituta ADP

Quantitative data will be coded and the identifying key (a list connecting names to numbers) will be kept in a separate, secure locked location in the field coordinator’s office. The data will be entered into a data-analytic computer program (e.g., SPSS), without the identifying key. Data will only be available to the members of the project group. No attributable data will be used in publications. The investigators will analyze the data, and both positive and negative trial results will be disclosed. Results will be submitted for publication to peer-reviewed scientific journals.

The qualitative research will follow thematic analyses as described above.

For the RCT’s, both intention-to-treat analysis and completers’ analyses will be carried out. To measure comparisons at baseline between the two treatment groups t-tests will be conducted for continuous variables and chi-squared test for categorical ones. Repeated measurement analysis will be carried out to assess differential change over time in mean GHQ-12 scores between groups. We will add the following covariates at baseline to examine subgroup effects: education, employment, and severity of symptoms. All analyses will be carried out in SPSS, with p-levels of <.05 indicating statistical significance.

For the economic evaluation, we follow the approach used before in a similar trial (Buttorff et al, 2012). The number of days with reduced working hours because of poor health will be calculated from the WHODAS-12. Participants’ self-reported their health-care utilization, medication use and out-of-pocket payments will be measured with the items derived from the SRI at post treatment and 3 months follow-up.

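### The sample-size inputs contradict each other: 133 per group gives power of about 0.90–0.92, not 0.95, for 50% vs 30%, and those are proportions while the primary outcome is a mean GHQ-12 score

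*Protocol*

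**What the plan says.** The Protocol, Methodology, under *Statistical power and sample size*, sets the target for the definitive trial (Study Phase 3) as a "50% reduction in GHQ-12 symptom score in the PM+ group as compared to a 30% reduction in the control group", 3 months on. It adds: "This corresponds with an odds ratio of for the PM+ intervention of 2,3". The result is "Power calculations suggest a minimum sample size of 133 participants per group (power = 0.95, alpha = 0.05, two-sided". Allowing for 30% attrition, the protocol plans 173 per group, 346 in all.

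The GHQ-12 entry under *Measures* makes the primary outcome the level of distress 3 months after the fifth session. It is the sum score, which "ranges between 0-36 with higher scores representing higher levels of distress". Under *Data Management and Statistical Analysis* the planned analysis is: "Repeated measurement analysis will be carried out to assess differential change over time in mean GHQ-12 scores between groups".

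**The concern.** Two things do not fit.

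- **The arithmetic.** The effect size, alpha, sidedness, power and sample size are all stated, so they can be checked against one another. They do not agree.
- **The scale.** A percentage reduction in a symptom score is a change in a mean, and a change in a mean has no odds ratio. An odds ratio belongs to a yes/no outcome, but the protocol defines and analyses a score.

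At stake is the power statement for the primary outcome of the definitive trial. As written it is too favourable for the comparison it describes. For the comparison the protocol plans, it gives no target difference to judge the sample size against.

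**Working it through.** **Inputs**, from *Statistical power and sample size* unless noted: p1 = 0.50, p2 = 0.30, odds ratio 2.3, two-sided alpha 0.05, power 0.95, n = 133 per group, attrition 30%, 173 enrolled per group. Allocation is 1:1 (*Procedure*, Randomization). The protocol gives no mean or SD for the GHQ-12.

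**Step 1: which reading gives the odds ratio?** (0.50/0.50)/(0.30/0.70) = 1/0.4286 = 2.33. The stated 2.3 therefore treats 50% and 30% as proportions.

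**Step 2: try to reproduce 133.** Pooled-variance formula, with mean proportion 0.40:

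n = [z(0.975)·√(2·0.40·0.60) + z(0.95)·√(0.50·0.50 + 0.30·0.70)]² / (0.50 − 0.30)²
= [1.960·0.6928 + 1.645·0.6782]² / 0.04 = 2.4735² / 0.04 = 152.95, so 153.

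Other two-sided formulas at power 0.95:

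| Formula | n per group |
|---|---|
| Unpooled variance | 150 |
| Pooled variance | 153 |
| Arcsine | 154 |
| Log odds ratio (2.33) | 159 |
| Pooled, continuity-corrected | 163 |

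None gives 133.

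**Step 3: power that 133 per group does give.** Pooled formula: [0.20 − 1.960·√(0.48/133)] / √(0.46/133) = 0.08226/0.05881 = 1.399, and Φ(1.399) = 0.919. Other two-sided methods:

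| Method | Power at 133 |
|---|---|
| Continuity-corrected | 0.898 |
| Fisher exact | 0.901 |
| Log odds ratio (2.33) | 0.910 |
| Arcsine | 0.919 |
| Exact chi-square | 0.922 |
| Unpooled | 0.925 |

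**Step 4: what could have produced 133?** At least two routes.

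- Two-sided 0.90: 133 is the smallest n at which Fisher's exact test reaches 0.90 (132 gives 0.898, 133 gives 0.901). The continuity-corrected formula gives 133.8, so 134.
- One-sided 0.05 with power 0.95, log odds ratio: (1.645 + 1.645)²·(1/0.25 + 1/0.21)/0.8473² = 132.08, so 133.

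Either the 0.95 or the word two-sided could be the wrong entry.

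**Step 5: power after the stated attrition.** 173 × 0.70 = 121.1, so 121 per group. Pooled formula: [0.20 − 1.960·√(0.48/121)] / √(0.46/121) = 1.242, power 0.893 (0.871 by Fisher exact).

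**Step 6: the planned scale.** For a two-sided two-sample comparison of means with 121 per group, the detectable standardised difference is about (1.960 + 1.282)·√(2/121) = 0.42 at 90% power. At 95% it is (1.960 + 1.645)·√(2/121) = 0.463, or 0.465 by the t distribution; d = 0.46 gives only 0.946, so the safe rounding is 0.47.

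If 50% vs 30% is read as a mean difference of 20% of the baseline mean, then d = 0.20/k, where k is the SD as a fraction of that mean. k is an assumption, because the protocol gives none. With 121 per group:

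| k | d = 0.20/k | Power (t test) |
|---|---|---|
| 0.40 | 0.50 | 0.97 |
| 0.45 | 0.44 | 0.93 |
| 0.50 | 0.40 | 0.87 |
| 0.60 | 0.33 | 0.73 |

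These are before any gain from baseline adjustment or repeated measures.

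**The case against.** The strongest reply is that little turns on this. Power for 50% vs 30% is 0.92 with 133 analysable, 0.89 with 121 and 0.97 if all 173 per group are retained, all respectable. No test, enrolment figure or participant risk changes, and a null result is read from the estimate and its confidence interval, not from planned power. All of that stands. It limits the consequence, but the 0.95 is still wrong as written.

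A second reply is that the responder reading is inferred, since the text speaks of a reduction in score. That is true, but it is the only reading that yields the stated odds ratio. A reading in terms of means has no SD with which to check 133.

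A third is that a responder definition or an SD may be in a statistical analysis plan, which is not shown. The point is therefore confined to the protocol. The protocol itself fixes the effect, the odds ratio, the sample size, the power and the analysis, and these do not fit together.

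Two stronger readings are tempting. A reader might infer that the trial is underpowered for its planned analysis. The protocol gives no SD, so that cannot be shown, and the result in Step 6 depends on the assumed spread. A reader might also infer that the authors simply used 0.90. Step 4 shows that a one-sided calculation at 0.95 fits equally well, so the cause is open.

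**Conclusion.** The power statement is wrong as written. For 50% vs 30% as proportions, two-sided 0.05 and power 0.95 need about 150 to 163 per group, against the 133 stated. The stated 133 gives about 0.90 to 0.92, a type II error of 8% to 10% where 5% is claimed. This rests only on the protocol's own inputs and on the reading that its odds ratio implies.

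Separately, the calculation is on a different scale from the protocol's primary outcome and analysis. Whether 346 is enough for the mean GHQ-12 comparison is undetermined, neither shown adequate nor shown inadequate.

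The 0.89 at 121 per group also reflects how 133 was inflated for attrition (133 × 1.3 = 173, whereas 133/0.70 = 190). That is a separate matter and does not add to the size of this one.

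**What to change.** Keep enrolment at 346 and change the wording of *Statistical power and sample size*:

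1. Replace the stated 0.95 with the power the design has for 50% vs 30%: about 0.92 with 133 analysable per group, and about 0.89 with the 121 per group expected after 30% attrition. Name the formula used.
2. Since the mean GHQ-12 score at 3 months is primary, drop the odds ratio. State the target difference in GHQ-12 points with an SD and its source, for example the Phase 1 pilot.
3. Add that 121 per group gives 90% power for a standardised difference of 0.42 and 95% for 0.47, before any gain from baseline adjustment.

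The cost is a protocol wording change and a less favourable stated power.

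### The 30% attrition allowance was added as 133 × 1.3 rather than 133 / 0.7, so 173 per arm leaves about 121 women per arm at 3 months, not 133; the cost in power is modest

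*Protocol*

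**What the plan says.** The section on statistical power and sample size (protocol, Methodology) builds the size of the definitive trial in three steps.

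- Effect: a "50% reduction in GHQ-12 symptom score in the PM+ group as compared to a 30% reduction in the control group", followed by "This corresponds with an odds ratio of for the PM+ intervention of 2,3".
- Base size: "Power calculations suggest a minimum sample size of 133 participants per group", with "power = 0.95, alpha = 0.05, two-sided".
- Allowance for loss: "Taking into account an expected 30% attrition at 3 months follow-up, we aim to include a total number of 346 participants", split as "173 in the PM+ group and 173 in the care-as-usual control group".

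The attrition is placed at the 3-month follow-up. The GHQ-12 description under Measures makes that same visit the time point of the primary outcome. The protocol gives no other attrition rate and no further reserve. The totals of 346 and/or 173 per arm recur in the Project summary, under Study Design and in the Methodology overview. The screening target of 3460 under Selection is derived from 346.

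**The concern.** The protocol calls 133 per group a minimum and says that the enrolment target takes the expected loss into account. A reader will conclude that 133 per arm should still be available at 3 months if 30% are lost. They will not be. The figure of 173 is what results from adding 30% of the evaluable number, whereas the loss is 30% of the larger, enrolled number.

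At stake is the truth of the sample-size justification for the primary time point: at its own attrition rate, the plan does not reach its own minimum. The design, the primary outcome and the planned analysis are not affected.

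**Working it through.** **Inputs.** From the section on statistical power and sample size: 133 per group required; power 0.95; two-sided alpha 0.05; attrition 30%; 173 per arm enrolled; effect 50% versus 30%; odds ratio 2.3. From the randomisation step under Procedure: 1:1 allocation.

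**1. Reproducing the stated target.** n × (1 + d) = 133 × 1.30 = 172.9, rounded up to 173 per arm, 346 in total. This matches the protocol exactly.

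**2. Target that keeps 133.** n / (1 − d) = 133 / 0.70 = 190 per arm, 380 in total, which is 34 more than 346. Check: 190 × 0.70 = 133.

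**3. What 173 delivers.** 173 × 0.70 = 121.1, so about 121 per arm. The shortfall is 133 − 121 = 12 per arm (12 / 133 = 9%). The largest attrition that still leaves 133 is 1 − 133/173 = 23.1%.

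**4. Power lost, taking 133 as giving 0.95.** With the effect held fixed, the noncentrality scales with the square root of n. At n = 133 it is 1.960 + 1.645 = 3.605. At n = 121 it is 3.605 × √(121/133) = 3.438. Power = Φ(3.438 − 1.960) = Φ(1.478) = 0.930. The loss is 2 percentage points.

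**5. Power lost, for 50% versus 30% as proportions.** The stated odds ratio fits this reading: (0.5/0.5) / (0.3/0.7) = 2.33. With the pooled normal formula and mean proportion 0.4,

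power = Φ{[0.20 × √n − 1.960 × √(2 × 0.4 × 0.6)] / √(0.5 × 0.5 + 0.3 × 0.7)} = Φ{(0.20 × √n − 1.358) / 0.678}.

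- n = 133: (2.307 − 1.358) / 0.678 gives power 0.919.
- n = 121: (2.200 − 1.358) / 0.678 gives power 0.893.

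The loss is 2.6 percentage points.

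**6. Separating the two gaps.** Solving the same formula for 0.95 gives n = (1.358 + 1.645 × 0.678)² / 0.20² = 153 per arm. So 133 per arm already falls short of 0.95 on this basis, before any attrition.

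| Basis | Power at 133 | Power at 121 | Due to the attrition slip |
|---|---|---|---|
| 133 taken to give 0.95 | 0.950 | 0.930 | 2.0 points |
| 50% versus 30% as proportions | 0.919 | 0.893 | 2.6 points |

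**The case against.** Four points can be made on the other side.

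- **Power remains good.** Even on the less favourable basis it is about 0.89, and the slip itself costs only 2 to 3 points. This stands, and it is why the matter is minor. It does not make the stated figures consistent.
- **Women lost by 3 months may still contribute.** The Data Management and Statistical Analysis section plans intention-to-treat and repeated-measures analyses, and there is a post-treatment GHQ-12. Depending on the method, earlier data could soften the loss. This stands in part, so 121 should be described as the number with 3-month data and not as the number analysed. The protocol, however, applies attrition directly to the 133, takes no credit for partial data, and also plans a completers' analysis.
- **The 0.89 is not the power of the planned analysis.** It treats the effect as two proportions, whereas the text speaks of a reduction in score and the analysis compares mean GHQ-12 over time. This stands, and any restated power must say so.
- **The whole drop from 0.95 to 0.89 might be read as the effect of attrition,** so that the type II error would go from 5% to about 11% because of this slip. The documents do not support that reading. On the basis that gives 0.89, the type II error is already about 8% with all 133 women present (1 − 0.919). The remaining gap arises because 133 does not follow from 50% versus 30% at 0.95, two-sided. On the protocol's own basis the slip takes the type II error from 5% to about 7%.

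**Conclusion.** The sample-size statement is wrong as written, and the error is minor. At 30% attrition, 173 per arm leaves about 121 women per arm with 3-month data, 12 below the protocol's minimum; 133 is protected only up to about 23% attrition. Power falls from 0.95 to about 0.93 if 133 is accepted as giving 0.95, or from 0.92 to 0.89 for 50% versus 30% as proportions.

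The counts rest only on the protocol's own figures and on attrition being a share of those enrolled and equal in both arms. The power figures also rest on the basis named for each and on only women with 3-month data counting.

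A reader might also infer that enrolling 190 per arm would restore the stated 0.95. That holds only if 133 does give 0.95. On the proportions basis, 190 enrolled and 133 retained give about 0.92. The origin of 133 is a separate question that this correction does not settle.

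**What to change.** Keep 346 and correct the sentence. State that 173 per arm with 30% attrition leaves about 121 per arm with 3-month data, and give the power with its basis: about 0.93 if 133 per arm gives 0.95, or about 0.89 for 50% versus 30% as two proportions at two-sided 0.05. Add that the latter is not the power of the planned repeated-measures analysis of mean GHQ-12.

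Alternatively, state that 173 per arm protects 133 per arm only up to about 23% attrition.

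Either restatement changes protocol wording only. It adds no participants or procedures and leaves the other mentions of 346 and 173 as they are. The cost is a less favourable stated power or attrition margin.

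If the sponsor prefers to retain 133 at 30% attrition, the target is 190 per arm (380 in total). At the protocol's assumed yield under Selection (20% positive, half of them willing, so 10%), that means screening 380 / 0.10 = 3800 women rather than 3460, and changing every place where 346 or 173 appears. This option should not be presented as restoring 0.95 on the proportions basis.

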Previous stressor exposure will be assessed using the Life Events Checklist (Gray et al., 2004). This is a widely used list of 17 experienced or witnessed events, such as rape, serious injury, combat exposure, or the sudden death of a loved one. A Kiswahili version of this list is available (Whetten et al., 2011). At post-test the question phrasing will be adapted to capture life events that have occurred since commencing in the trial.

1. WHO Violence Against Women Instrument (WHO-VAW)

This study uses 5 key questions of the WHO Violence Against Women Instrument (WHO-VAW, WHO, 2003) as developed for use in the WHO Multi-Country Study on Women’s Health and Domestic Violence (WHO, 2005) and will adhere to the WHO ethical guidelines for the conduct of violence against women research, which stress confidentiality and privacy, and availability of referral for psychological and social help. The WHO Multi-Country Study on Women’s Health and Domestic Violence was conducted among 24 000 women in 10 countries, including Swahili-speaking Tanzania, and accordingly a Swahili version exists (WHO, 2005).

1. PCL-5: PTSD symptoms

Posttraumatic stress disorder (PTSD) symptoms will be measured using the PTSD Checklist for DSM-5 (PCL-5) (PCL-5; (Weathers et al, 2013), which is a 20-item checklist corresponding with the 20 DSM-5 PTSD symptoms. Items are rated on a 0-4 scale and add up to a total severity score of 80. The PCL-5 will be adapted to ask for symptoms in the last week (rather than month) to enhance sensitivity to change.

1. SRI: cost of care

The Service Receipt Inventory (SRI) was developed for the collection of data on service utilization and related characteristics of people with mental disorders, as the basis for calculating the costs of care for mental health cost-effectiveness research, including in low and middle income countries (Chisholm, Knapp, et al., 2000). Selected items from the SRI will be included, i.e., health seeking at the hospital, and from traditional healers.

*The PM+ intervention program:*

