- ‘Strengthening Social Support’ (20 minutes)
- Practice ‘Managing Stress’ (10 minutes)
- Set practice tasks and end the session (5 minutes)

Session 5:

- During program assessment general review of the past week (5 minutes)
- Discussion and education about how to stay well (30 minutes)
- Review PM+ strategies (30 minutes)
- Post-program assessment (20 minutes)
- Ending the session and program (5 minutes)

*Assessment as part of PM+:*

At the beginning of each PM+ session, participants will also be administered the Psychological Outcome Profiles instrument (PSYCHLOPS; [Ashworth, 2004](#_ENREF_2)) by their PM+ provider. PSYCHLOPS consists of four questions. It contains three domains: problems (2 questions), function (1 question) and wellbeing (1 question). Participants are asked to give free text responses to the problem and function domains. Responses are scored on an ordinal six-point scale producing a maximum score of 18 (6 points per domain). The peri (during)- and post-therapy versions of PSYCHLOPS consists of the same four questions but adds an overall valuation question (determining self-rated outcome ranging from “much better” to “much worse”). PSYCHLOPS has been validated in primary care populations across several countries (Czachowski, Seed, Schofield, & Ashworth, 2011; Heoinsson, Kristjansdottir, Olason, & Sigurosson, 2013).

*Enhanced Treatment-as-usual (TAU)*

Treatment-as-usual in these clinics in primary healthcare centres (PHCs) in Nairobi, Kenya to individuals with common mental disorders often consists of no treatment. For this study, participants in the TAU group will be referred to their primary care clinicians (usually nurses) for follow-up. These primary care nurses will have received the standard International Federation of Red Cross training in supportive counselling and psychological first aid (WHO, WTF, WVI, 2011) to enhance usual care.

If, during this treatment or during the study’s assessments participants in TAU arm show severe psychiatric disorders (eg psychosis) or problems (e.g., suicidality) that require immediate specialist treatment and follow-up, they will be referred to the subcounty hospital.

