Of note, in Nairobi, each primary health care facility, and sub-country hospital, employs a Community Health Extension Worker (CHEW), who coordinates referrals from within the community and to ensure patients are followed-up by nurses and/or Community Health Workers (CHWs). The CHEWs from each health facility of the project is working with will be receiving a small additional allowance for their involvement in the research project. Their involvement will be to monitor that referred patients are actually seen when they are referred to the enhanced usual care or to the subcounty office. The CHEW will complete a basic form to monitor the date, time of the appointments and whether they occurred.

Throughout the trial, we will carefully keep track of the types and amount of support received through SRI items (see measures section above).

*PM+ providers and protocol adherence:*

PM+ providers will be female CHWs, who were recommended by the Ministry of Health, based on those that have shown high performance in their regular health work in the communities. After receiving the recommendation, CHWs will be selected based on individual interviews.

PM + providers will meet the following criteria:

- High school diploma (form 4 level of education or above);
- Reasonable proficiency in both Kiswahili and English language – written and verbal;
- 1-year training post-secondary school as CHWs or health related career;
- 2-years and above experience in community work;
- Already working as a CHW within a given geographical area.

PM+ providers will receive 2 weeks of training. In addition, one professional supervisors will be employed for each of the 3 health facility areas. Protocol adherence will be ensured by the supervisors and weekly group supervisions of the CHWs (Murray et al, 2011). Supervisors will then receive their own supervision and on-the-job training in supervision skills by the project lead consultant, who is a qualified counselling psychologist and available for any specific and/or urgent cases where either the CHWs themselves, the supervisors or any of the clients in the program need support. This will take place weekly as well.

To ensure adherence to the PM+ manual and ensure fidelity of interventions, 10% of all PM+ sessions will be attended by the supervisor, using a checklist to ensure basic elements of the PM+ intervention have been followed as required.

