For the costs analysis, two types of costs measured at post-treatment and at the 3-months follow-up will be estimated based on SRI scores: health-system costs (i.e., costs related to the intervention itself and associated medications and/ or clinical investigations) and the "time costs" for the subjects and their families (i.e. time spent travelling to, waiting for or receiving care, plus the wages from any days of work lost). The human resource use associated with the community health workers employed in the intervention will be estimated by multiplying the time a participant in PM+ has contact with a CHW by the per-hour cost of the CHW.

Costs, scores and days-of-work data from each follow-up will be summed to give totals for the 3 months post-treatment. Differences between PM+ and TAU, will be assessed using generalized linear models. Cost–effectiveness acceptability curves showing the probability that an intervention remains relatively cost–effective at increasing monetary values, will be developed.

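### The SRI item list stops at hospital and traditional healers, so as written it leaves the primary care nurse contacts of enhanced usual care out of the SRI-based cost comparison and contradicts the protocol's other accounts of the SRI

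*Protocol*

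**What the plan says.** The Measures section (item on the SRI, cost of care) describes the content of the instrument in one sentence: "Selected items from the SRI will be included, i.e., health seeking at the hospital, and from traditional healers".

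Three other places describe what the SRI is to deliver.

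- Enhanced Treatment-as-usual: the trial will keep track of the "types and amount of support received through SRI items (see measures section above"), which sends the reader back to the list just quoted.
- Data Management and Statistical Analysis, economic evaluation: self-reported "health-care utilization, medication use and out-of-pocket payments will be measured with the items derived from the SRI".
- The same section, costs analysis: two cost types are to be estimated from SRI scores. One is "health-system costs (i.e., costs related to the intervention itself and associated medications" or investigations. The other is the time cost to women and families, including travel, waiting, receiving care and lost wages.

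On the comparator, "participants in the TAU group will be referred to their primary care clinicians (usually nurses) for follow-up". Safety Considerations adds that women in both arms can use this enhanced care.

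The only staff-time rule is for the intervention: "multiplying the time a participant in PM+ has contact with a CHW by the per-hour cost of the CHW".

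There is one other record of usual-care contacts: "The CHEW will complete a basic form to monitor the date, time of the appointments and whether they occurred". Its stated purpose is to monitor that referred patients are seen.

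**The concern.** Cost-effectiveness and health care costs are both part of the first specific objective. An incremental cost needs resource use measured in the same way in both arms. Here the comparator consists of primary care contacts, and the itemised SRI content does not include them. A health economist who builds the questionnaire from the Measures section would collect hospital and healer use, cost the CHW hours of PM+, and have no SRI data on the care to which the control arm is referred. The woman's own travel and waiting time for those visits would be lost too, because time costs also come from the SRI.

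An analysis plan can supply a unit cost later. It cannot supply visits that nobody asked about, so the item list needs to be right before data collection.

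**Working it through.** There is no plan figure to reproduce, because the documents give no visit rates and no unit costs. The check is a comparison of texts, followed by the algebra of what is left out.

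**1. Scope of the SRI, place by place**

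| Place in the protocol | Hospital | Healers | Primary care nurse | Medication | Out-of-pocket | Travel/waiting time |
|---|---|---|---|---|---|---|
| Measures, SRI | yes | yes | not listed | not listed | not listed | not listed |
| Enhanced TAU | implied | implied | implied (all support) | – | – | – |
| Economic evaluation | implied | implied | implied (utilization) | yes | yes | – |
| Costs analysis | – | – | – | yes | – | yes |

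The first row cannot deliver the other three.

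**2. Does hospital include the nurses?** Not on this protocol's usage. It states that "each primary health care facility, and sub-country hospital, employs a Community Health Extension Worker", naming the two as separate places. Control women go to primary care clinicians; only severe or urgent problems go to the sub-county hospital.

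**3. What the costing picks up.** The PM+ side is well defined. The itemised minutes sum to 90 in each of the five sessions (session 1, for example: 30 + 20 + 20 + 15 + 5), so 5 × 90 = 450 minutes, or 7.5 CHW hours per completer. For primary care contacts there is no listed SRI item and no named staff-time rule in either arm.

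**4. Effect on incremental cost.** Let n_P and n_T be the mean primary care visits per woman in PM+ and TAU, and c the cost of a visit, including the woman's time. If the visits are not collected:

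true incremental cost = measured incremental cost + (n_P − n_T) × c

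- n_T > n_P: the measured figure overstates the incremental cost of PM+.
- n_T = n_P: no error.
- n_T < n_P: the measured figure understates it.

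None of n_P, n_T or c is in the documents.

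**5. If the appointment form were used alone.** It covers referred patients. Control women are referred; PM+ women have access, but no routine referral is described for them. Visits would then be counted mainly in TAU, leaving an error of about n_P × c in the opposite direction: PM+ would look too cheap.

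**6. Recall window.** The post-treatment assessment is 7 weeks after baseline and 1 week after session 5, which puts session 5 at about week 6. Adding 3 months (about 13 weeks) gives about week 19. One SRI at 3 months would therefore cover about 19 weeks. If the SRI is also taken post-treatment, as the economic section says, the windows are about 7 and 19 − 7 = 12 weeks. The measures matrix leaves the post-treatment SRI cell blank; that is a separate point, but it decides which window applies.

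**The case against.** The strongest reply is that the actual questions are in Annex 6, which is not available here. One summary sentence may simply be loose, and three other places point to wider collection. That is a fair limit on the harm. If the annex already holds a primary care item, the work reduces to correcting the sentence and the costing text. The contradiction in the protocol would remain.

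Second, the appointment form already gives a prospective count for referred women, so control-arm contacts are not unrecorded. This stands. A missing contact length is also no obstacle, since visits can be multiplied by a cost per visit. What the form does not do is cover women who were not referred, capture their time, or feed into the costing by any stated route.

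Third, a unit-cost rule for each service is commonly left to an analysis plan. This also stands: the missing nurse rule would not be a finding alone. It matters here because it sits beside a data-collection gap and a rule that names CHW time only.

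A reader might infer that the design makes PM+ look too expensive, since control women are the ones sent to nurses. The documents do not support that. They give no uptake in either arm, describe usual care as often amounting to no treatment, and open enhanced care to both arms; if only the form were used, the error would run the other way. Nor can a percentage bias be derived by setting nurse hours against the 7.5 CHW hours: both the nurse-to-CHW cost ratio and the difference in contacts would have to be invented, and CHW time is only part of incremental cost.

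**Conclusion.** The inconsistency is real and can be read from the text: the SRI list is narrower than three other statements of what the SRI measures, and it omits the care that defines the comparator. If the list is followed, the SRI-based comparison lacks primary care contacts and the associated patient time, while PM+ provider time is costed.

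The direction and size of the error in incremental cost are undetermined. It equals the between-arm difference in visits times the cost per visit, and is zero if use is equal. The practical consequence rests on one assumption, that Annex 6 follows the Measures sentence. The GHQ-12 analysis and the other clinical outcomes are untouched. This should be corrected before data collection, but it bears on the economic evaluation only.

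**What to change.** In the Measures section, replace the two-item list with one covering primary care nurse or clinician visits (number, with travel and waiting time), hospital use, traditional healer use, medication and out-of-pocket payments. Ask the items identically in both arms at every scheduled SRI assessment, after GHQ-12, WHODAS and PCL-5. Check that Annex 6 contains the same items. A nurse item alone would not be enough, because the medication, payment and time data promised in the analysis section would still be missing from the list.

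In the costs analysis, add that primary care visits are costed in both arms as number of visits × unit cost. Use the appointment form as a cross-check on attendance among referred women, not as the main source.

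The cost is a few extra questions at assessments that already take place, and one unit cost. The downsides are recall error, over about 19 weeks if the SRI is asked only at 3 months, and a small risk that an answer reveals allocation to the blinded assessor. Placing the items after the outcome scales limits that risk.
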